### Randomization

Participants will be stratified by stroke type and randomly allocated to either the RAGT or CGT group using a computer-generated permuted block randomization method with permuted block sizes of two and four. Random allocation will be performed by an independent researcher not involved in the assessments, using the Research Electronic Data Capture tool [24].

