### Outcomes

#### Feasibility assessment

Following prior recommendations [28], we will assess the feasibility of this pilot study based on the following indicators: (i) recruitment and enrollment rates, defined as the average number of participants enrolled in the study per month; (ii) enrollment rate, defined as the proportion of individuals who consent to participate among those who meet the eligibility criteria during the preintervention assessment; (iii) adherence rate, defined as the proportion of participants who complete the intervention according to the schedule, serving as an indicator of the intervention’s acceptability; and (iv) retention rate, defined as the proportion of participants who complete outcome measures from baseline to predischarge assessment.

These measures will serve as progression criteria to determine whether to proceed with the study [29]. The specific criteria are as follows: (i) recruitment rate of at least 0.8 participants per month; (ii) enrollment rate of at least 90% of screened eligible individuals consenting to participate [30]; (iii) adherence rate, with at least 90% of participants completing scheduled training times [30]; and (iv) retention rate, with a minimum of 90% of enrolled participants completing all outcome measures until follow-up [30, 31]. Recruitment rate criteria were established based on our institution’s experience, while enrollment, adherence, and retention rates were determined with reference to similar previous studies on RAGT [30, 31]. Even if a participant fails to meet any of the four established criteria, the study will proceed with protocol modifications if the underlying issues can be addressed [29].

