In addition, to understand participant characteristics, the following data will be collected at baseline: age; sex; height; weight; disease type; affected side; days post-stroke onset at admission, assessment, and discharge; National Institutes of Health Stroke Scale (NIHSS) score; GCS score; SIAS motor function scores for the lower extremities; trunk function; sensory function in the lower extremities; tone in the lower extremities; function in the lower extremities on the unaffected side; and visuospatial function. The NIHSS is a reliable and validated index for assessing stroke severity [39–41]; it evaluates consciousness, gaze, visual field, facial paralysis, paralysis of the extremities, ataxia, sensory disturbance, aphasia, dysarthria, elimination issues, and neglect, with scores ranging 0–42. A score of 0 is considered normal, while 42 indicates the most severe condition. The GCS consists of three items, namely eye opening, verbal response, and motor response. Eye opening is scored from 1 to 4, verbal response from 1 to 5, and motor response from 1 to 6. The total GCS score is defined as the sum of the scores of these three items, ranging 3–15, with 3 indicating severe impairment and 15 indicating normal responsiveness.

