### Sample size

This is a pilot study; therefore, the sample size was not calculated based on statistical testing power [16]. We aim to enroll 32 participants, as this is presumed to be an adequate sample size for gathering insights on recruitment, enrollment, adherence, and retention rates. With 32 participants recruited, a retention of 90% can be estimated to within a 95% confidence interval (CI) ranging from 75–96%. This sample size should also suffice to accurately assess means and variances [42] and to provide data regarding clinical outcomes.

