### Analytical methods

Feasibility results will be reported using descriptive statistics. Recruitment, enrollment, adherence, and retention rates will be computed with 95% confidence intervals. The adverse events and their frequencies will be recorded. Any exclusions or dropouts, along with their reasons and stages of occurrence, will also be recorded. The success of blinding will be detailed as a percentage of correct guesses.

The primary outcome measure will be the incidence of gait independence during the intervention period. The cumulative incidence of gait independence will be analyzed using the Kaplan–Meier method, and the log-rank test will evaluate the significance of differences in the Kaplan–Meier curves between groups. Cumulative incidence of gait independence events at the end of the intervention, along with the median duration from baseline to gait independence attainment, and the restricted mean survival time until the end of the intervention will be calculated. Additionally, to supplement the initial treatment effect analysis, differences will be evaluated using the generalized Wilcoxon test. Individuals who do not achieve gait independence during the intervention period will be censored. Secondary clinical outcomes will encompass gait performance measures, physical function, and activity outcomes at baseline, 4 weeks, 8 weeks, and discharge, alongside the intervention dose. Comparisons between the two groups will utilize the chi-square test for categorical variables and either Student’s *t-*test or Mann–Whitney *U* tests for continuous variables. To evaluate the potential effectiveness of the intervention and gather data useful for future trial design, we will estimate the effect size for the time elapsed from baseline to achieving gait independence, specifically estimating the hazard ratio as a relative measure of the likelihood of achieving gait independence over time.

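### SIAS and FIM scores are to be compared with unadjusted two-group tests although baseline values are collected; adjusting for baseline and stroke type would gain precision at almost no cost

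*Protocol article*

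**What the plan says.** Clinical outcomes in the protocol article names SIAS lower-limb motor score, SIAS trunk score and FIM total among the secondary outcomes. Analytical methods then schedules gait performance, "physical function, and activity outcomes at baseline, 4 weeks, 8 weeks, and discharge". Its next sentence gives the method: "Comparisons between the two groups will utilize the chi-square test for categorical variables and either" Student's t or Mann–Whitney U for continuous variables. It mentions no covariate, change score or longitudinal model for these outcomes.

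Baseline values are available. The participant characteristics to be collected at baseline, listed at the end of Clinical outcomes, include "SIAS motor function scores for the lower extremities; trunk function". FIM is not in that list, but Analytical methods includes activity outcomes at baseline, which covers it.

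Under Randomization, "Participants will be stratified by stroke type and randomly allocated to either the RAGT or CGT group". Stroke type is the only stratification factor, so the design does not balance baseline SIAS or FIM. Under Sample size, "We aim to enroll 32 participants", and "the sample size was not calculated based on statistical testing power".

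**The concern.** A follow-up SIAS or FIM score depends partly on where the patient started. A two-sample test on the follow-up score leaves that known variation in the error term, and it ignores the factor used to stratify the randomisation. In a trial this small, the arms can differ noticeably at baseline by chance, and part of that difference then appears as an apparent treatment effect.

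What is at stake is precision, and bias in those trials that happen to be imbalanced. A secondary matter is what the pilot passes on. Sample size says the 32 participants should suffice to assess means and variances, and the Discussion intends to use variability estimates for the next trial. If that trial adjusted for baseline, it would need the residual SD and the baseline–outcome correlation, and the named tests produce neither.

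The article itself names the tests, so this is a stated method and not a detail left to an unseen analysis plan.

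**Working it through.** **1. The plan's own figure.** The only sample-size figure is that "a retention of 90% can be estimated to within a 95% confidence interval (CI) ranging from 75–96" per cent. The Wilson interval with p = 0.90, n = 32 and z = 1.96 has
- centre (0.90 + 3.84/64) / (1 + 3.84/32) = 0.857;
- half-width 1.96 × √(0.09/32 + 3.84/4096) / 1.12 = 0.107.

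This gives 75.0% to 96.4%, which matches. The sample-size statement is not in question.

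**2. Inputs for the comparison.**
- n = 32 (Sample size), taken as 16 per arm. The ratio is not stated in words; 1:1 is assumed from two arms and block sizes of two and four.
- The baseline–outcome correlation r is not given. The range 0.3 to 0.7 is assumed.
- Two-sided 5% and 80% power are assumed for the detectable difference. The plan makes no power claim, so this is only a yardstick.

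**3. Gain from adjustment.** Relative to the unadjusted comparison, ANCOVA multiplies the variance of the group difference by 1 − r². The equivalent unadjusted sample is 32/(1 − r²). The unadjusted detectable difference is (1.96 + 0.84) × √(2/16) = 0.99 SD, and adjustment multiplies it by √(1 − r²).

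| r | variance left | variance cut | equivalent n | detectable difference (SD) |
|---|---|---|---|---|
| unadjusted | 1.00 | – | 32 | 0.99 |
| 0.3 | 0.91 | 9% | 35 | 0.94 |
| 0.5 | 0.75 | 25% | 43 | 0.86 |
| 0.6 | 0.64 | 36% | 50 | 0.79 |
| 0.7 | 0.51 | 49% | 63 | 0.71 |

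The progression criterion is a "retention rate, with a minimum of 90% of enrolled participants completing all outcome measures until follow-up". At 90%, about 14 per arm remain (0.9 × 32 = 28.8). The detectable difference is then 1.06 SD unadjusted, and 1.01, 0.92, 0.85 or 0.76 SD adjusted.

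**4. Price of estimating the covariate.** One baseline covariate inflates the variance by 1 + 1/(32 − 4) = 1.036, or just under 2% of the standard error. Dividing the equivalent sizes by 1.036 gives about 34, 41, 48 and 61. Stroke type takes a second degree of freedom. Stratified blocks keep it nearly balanced, so it should add little further inflation.

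**5. Chance imbalance.** The baseline difference between arms has standard error √(2/16) = 0.354 SD. A gap above 0.5 SD is therefore 0.5/0.354 = 1.41 standard errors, and arises in about 16% of trials of this size. It shifts the unadjusted follow-up difference by 0.5r: 0.15 SD at r = 0.3, 0.25 SD at r = 0.5 and 0.35 SD at r = 0.7.

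In 40,000 simulated normal trials with 16 per arm and no treatment effect, the unadjusted t-test rejected in 5.0% (r = 0.5) and 4.9% (r = 0.7) of all trials. Among trials with a baseline gap above 0.5 SD, it rejected in 12% and 18%.

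**6. Change scores do not remove the point.** The article does not say whether the scores are analysed as observed or as change; as observed is the plain reading. A t-test on change has variance factor 2(1 − r): 1.40, 1.00, 0.80 and 0.60 at the four correlations. Each is larger than the ANCOVA factor, and below r = 0.5 change is worse than the plain comparison.

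**The case against.** The strongest reply is that these are secondary outcomes in a pilot without a power calculation, that the Discussion calls the clinical findings exploratory, and that the planned tests are valid. All of that stands and keeps the point modest. A reader might infer that the comparisons have an inflated false-positive rate. The simulation shows they do not: the excess arises only given a chance imbalance, and the carry-over is r times the gap, not the whole gap.

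The size of the gain is also assumed throughout. Entry requires a SIAS lower-limb motor total of 6 or less on a 0–15 scale, which narrows the baseline range and may lower r for that score. At r = 0.3 the gain is about two participants after the cost of the covariate.

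Four stronger readings are tempting, and the article does not support them.
- **Baseline is tested.** The text lists baseline among the time points and then names the tests, so it can be read that way, but it does not say that a test is run at baseline or at every visit.
- **The next trial would be mis-sized.** Clinical outcomes treats gait independence as the leading candidate endpoint for later trials, and the effect size to be estimated is a hazard ratio. Nothing says that SIAS or FIM SDs will set the next sample size. A residual SD can still be computed from the collected data.
- **Chi-square is unsafe with 16 per arm.** The article names no categorical secondary outcome, so there is no variable to which this applies.
- **The choice between t and Mann–Whitney will be made after seeing the data.** The article does not say so. How the choice is made is detail that an article may leave to a fuller document.

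**Conclusion.** The point holds as one of efficiency and of bias given chance imbalance. The article fixes unadjusted comparisons for SIAS lower-limb motor, SIAS trunk and FIM total, and leaves unused both the baseline scores and the stratification factor. Depending on an assumed correlation of 0.3 to 0.7, adjustment removes about 9% to 49% of the variance of the group difference, or somewhat less after the degrees of freedom spent. The SIAS motor score may be near the lower figure.

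The conclusion rests on 1:1 allocation, on a roughly linear baseline–outcome relation, and on FIM being measured at baseline. The last of these rests on the mention of activity outcomes at baseline, since Fig. 4 is not shown. The consequence for the next trial is small. The change is worth making because it is nearly free.

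**What to change.** In Analytical methods, replace the two-sample tests for SIAS lower-limb motor, SIAS trunk and FIM total with the following:
- At 4 weeks, 8 weeks and discharge, estimate the group difference with its 95% CI by ANCOVA, with the baseline value of the same score and stroke type as covariates.
- Use a rank-based version for the trunk score if it takes only a few values; the article does not give its range.
- Report the residual SD and the baseline–outcome correlation for each score, so that a later trial can use them.
- Report baseline values descriptively by arm, and say that they are not tested.
- Confirm in the list of baseline data that FIM is recorded.

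The change should not extend to the 10-m and 6-min walk tests or to step counts. Entry requires an FAC of 1 or less, so a usable walking baseline is unlikely, and steps during training have no baseline.

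The cost is two degrees of freedom per model and a few sentences of text. No new data are needed.

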## Discussion

A systematic review and meta-analysis demonstrated the effectiveness of early repetitive gait training in enhancing gait independence in patients with stroke [43]. RAGT facilitates intensive, repetitive, and task-oriented training for individuals with hemiparetic stroke by partially or completely supporting their weight and movement through a robotic control mechanism [9]. Therefore, various reports have indicated that RAGT also facilitates repetitive gait training for individuals with stroke who are unable to walk [6, 7].

The objectives of this pilot study are as follows: (i) to evaluate the feasibility of performing a randomized controlled trial on RAGT for improving gait ability following acute stroke and (ii) to obtain preliminary estimates of the potential efficacy of RAGT for improving gait independence during the acute phase. These findings will inform decisions related to the feasibility of future trials and, if necessary, guide protocol revisions. Potential adjustments could encompass modifying eligibility criteria to improve recruitment and enrollment rates, refining intervention parameters to boost adherence, or revising assessment schedules to address retention rates.

There are certain limitations of this trial protocol. First, the trial protocol is based on a small sample size, which may not provide sufficient statistical power to evaluate the effectiveness of the intervention conclusively. Therefore, the findings related to clinical outcomes should be interpreted as exploratory in nature. To address this, future studies should include a larger sample size to increase statistical power and the reliability of results, potentially through multi-center trials. Rather than directly using effect sizes obtained from this study to determine the sample size for a future definitive trial, we intend to use estimates of variability and feasibility indicators—including recruitment, adherence, and retention rates—as well as the minimally important difference, if identifiable, to inform future trial designs [44]. Second, the absence of long-term follow-up assessments in this pilot study limits the ability to evaluate the sustainability of intervention effects, including their impact on long-term functional independence and overall health. Future definitive trials should incorporate follow-up assessments beyond discharge to assess the durability and long-term outcomes of RAGT.

To the best of our knowledge, this will be the first study to investigate the effects of RAGT on gait independence improvement in individuals with acute stroke. We posit that RAGT will enhance gait independence in this population, and the comprehensive results of this investigation and future large-scale trials will constitute essential evidence regarding the potential benefits of RAGT as an intervention for individuals with acute stroke.

## Trial status

### Protocol information

Protocol version number: 4.0Protocol version date: August 22, 2024.

### Recruitment timeline

Recruitment start date: December 1, 2023.Expected recruitment completion date: March 31, 2026.

## Data Availability

The dataset is accessible only to authorized research personnel; however, the data used and analyzed in this study can be provided upon reasonable request to the corresponding author.

## Abbreviations

CGT: Conventional gait training
FAC: Functional Ambulation Category
FIM: Functional Independence Measure
GCS: Glasgow Coma Scale
NIHSS: National Institutes of Health Stroke Scale
RAGT: Robot-assisted gait training
SIAS: Stroke Impairment Assessment Set
